**Secondary analysis:**

The secondary endpoint of this study is the immunogenicity after vaccination, which is performed on the FAS and PPS.

The antibody-positive rates at each follow-up point in the two groups will be statistically described as categorical variables, and Pearson’s chi-square test or Fisher’s exact test will be used for intergroup comparisons. The antibody titers at each follow-up point in the two groups will be statistically described as continuous variables, and the Mann–Whitney U test will be employed for intergroup comparison. For the absolute titers of neutralizing antibodies and anti-RBD antibodies, the median values of antibody titers will be calculated for the two groups at each follow-up point, as well as the corresponding intergroup differences and 95% CIs. For the relative titer values of variant-specific neutralizing antibodies, the geometric mean of the antibody titers for the two groups will be determined at each follow-up point, as well as the corresponding intergroup differences and 95% CIs.

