# 2. INTRODUCTION

## 2.1. Background

Coronavirus disease 2019 (COVID-19), an emergent acute respiratory infectious disease, has caused unprecedented morbidity and mortality during the pandemic^[1-2]^. Current drug treatment options are limited, making the establishment of an immune barrier through safe and effective vaccination a crucial strategy to control the virus’s spread^[3-4]^. The focus of vaccine research and development is on preventing antibody-mediated infection enhancement and vaccine-enhanced disease. Globally, 83 vaccines are undergoing clinical trials, with 184 vaccine candidates in preclinical evaluation^[5]^. Five technical routes for vaccine development are being pursued in China: inactivated, adenovirus vectors, recombinant subunits, nucleic acids, and attenuated influenza virus vectors. Five novel coronavirus vaccines have been conditionally marketed for emergency use^[6]^. Considering the “safety of the vaccine itself,” the Chinese Center for Disease Control and Prevention’s Novel Coronavirus Vaccine Working Group has drafted “Technical Guidelines for Novel Coronavirus Vaccination,” which outlines 31 conditions for vaccination. According to the National Health Commission, as of June 29, 2022, China has received over 1.2 billion doses of the COVID-19 vaccine, aiming to vaccinate at least 70% of the target population by the end of 2022, gradually establishing a herd immunity barrier.

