## 3.2. Eligibility criteria

### 3.2.1. Inclusion criteria

1. Signed informed consent;
2. In females, the urine pregnancy test was negative;
3. At least 6 months of follow-up was completed;
4. HBsAg, anti-HCV, HIV, treponema pallidum hemagglutination assay (TPHA) screening was negative;
5. Armpit temperature was ≤37.0℃;
6. The young group was aged 18–59 years, and the elderly group between 60–80 years.

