### 3.2.2. Exclusion criteria

1. In females, the urine pregnancy test positive;
2. Pregnant or lactating women;
3. Known allergies to certain components of these two vaccines;
4. Patients with serious chronic diseases or advanced diseases such as high blood pressure, diabetes, asthma, thyroid disease, etc. which cannot be controlled by drugs;
5. Those suffering from thrombocytopenia, hemorrhagic disease or thrombotic disease;
6. Those with congenital or acquired angioedema/neuroedema;
7. Those with a history or family history of convulsions, epilepsy, encephalopathy, other progressive neurological diseases, and psychiatric disorders;
8. Lymphadenopathy；
9. Lymphoma, leukemia and other systemic malignancies;
10. Autoimmune disease;
11. Chronic diseases with cute exacerbation or acute infectious diseases and fever.

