### 3.4.2 Secondary endpoint measures

- Immune protection of the participants:
  - - The titers of neutralizing and anti-receptor binding domain (RBD) antibodies at the baseline and the 1^st^, 2^nd^, 4^th^, 7^th^, 8^th^, 10^th^, 13^th^, and 16^th^ months after the first vaccination in each study group.

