# Including hepatitis B serologic, alpha-fetoprotein (AFP), carcinoembryonic antigen (CEA), Anti-HCV, HIV antibody, TPHA, electrocardiogram (ECG), chest x-ray, abdominal ultrasound (liver, gallbladder, spleen, pancreas, kidney). * Including liver and kidney function, blood glucose, and blood lipids.

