## 3.7. Recruitment

Participants will be recruited exclusively from two designated COVID-19 vaccination hospitals: the Fifth Medical Center of Chinese PLA General Hospital, Beijing; and the Hunyuan County People's Hospital, Shanxi Province. No other recruitment strategy (*e.g.*, advertisement) will be adopted in this study.

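### The old-young antibody comparison makes no use of the Day 0 titres, so any antibody present before dose 1 stays in the post-dose rates and titres and could bias the contrast if prior exposure differs by age

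*Protocol*

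**What the plan says.** **Entry.** Section 3.2.1 lists the infection screen: "HBsAg, anti-HCV, HIV, treponema pallidum hemagglutination assay (TPHA) screening was negative". In section 3.2.2 the only items touching vaccines or infection are "Known allergies to certain components of these two vaccines" and, within the last criterion, "acute infectious diseases and fever". The screening tests in the footnote to the schedule (section 3.5) are described as "Including hepatitis B serologic, alpha-fetoprotein (AFP), carcinoembryonic antigen (CEA), Anti-HCV, HIV antibody, TPHA", followed by ECG and imaging. None of these concerns past SARS-CoV-2 infection or an earlier COVID-19 vaccine dose. Sections 3.3.1 and 3.3.2 number the inactivated injections as doses one and two, starting at baseline, which implies previously unvaccinated participants without making it a criterion.

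**Measurement.** Section 3.4.2 includes "The titers of neutralizing and anti-receptor binding domain (RBD) antibodies at the baseline", and the schedule places humoral immunoassays at V1 (Day 0).

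**Analysis.** Section 3.10.1 defines the FAS by completion of three doses and the PPS by number of follow-ups attended. The Secondary analysis in section 3.10.2 says "The antibody-positive rates at each follow-up point in the two groups will be statistically described as categorical variables" and tests them between groups by chi-square or Fisher. It compares absolute titres by Mann-Whitney, with medians per group. It has no seroconversion, fold rise, baseline adjustment or baseline-negative subset. The Demographic analysis does not name serostatus among the variables used to judge comparability. The pseudovirus analysis of positive rates and titres follows the same method.

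**The concern.** Section 2.2 makes immunogenicity in the elderly part of the aim, and the young group is its comparator. A post-dose positive rate mixes two sources: antibody raised by the study vaccines and antibody that was there before. In a randomised comparison the second source would balance on average. Here the groups are defined by age, so nothing in the design balances it.

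If prior exposure were more common in one age group, that group would look more immunogenic, or a true deficit in the other would be exaggerated or masked. The effect would be largest where naive positivity is low, that is, early in the schedule or after waning. The data needed to see and remove the problem are already collected; what is missing is a rule that uses them.

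**Working it through.** **Inputs from the protocol.** Target sizes are 200 elderly and 100 young (section 3.6; 200 + 100 = 300, ratio 2:1). Tests are two-sided at 0.05 (section 3.10.2). The protocol gives no power, effect size, positive rate or share with prior exposure, so there is no stated figure to reproduce on this point.

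**Assumptions.** The naive positive rate q is the same in both age groups, so there is no true difference. Everyone with prior exposure is positive at the visit considered. The shares with prior exposure are p_Y (young) and p_E (elderly). The target sizes are used as if fully achieved in the analysis set.

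**Formula.** Observed rate = p + (1 − p)q. Spurious gap (young minus elderly) = (p_Y − p_E)(1 − q).

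Example with q = 0.30:
- Young at 20%: 0.20 + 0.80 × 0.30 = 0.44.
- Elderly at 5%: 0.05 + 0.95 × 0.30 = 0.335.
- Gap: 0.15 × 0.70 = 0.105, or 10.5 points.

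**How often the test would declare a difference.** For the same example:
- Pooled rate = (100 × 0.44 + 200 × 0.335)/300 = 0.37.
- Null SE = √[0.37 × 0.63 × (1/100 + 1/200)] = 0.05913.
- SE under the mixed rates = √[0.44 × 0.56/100 + 0.335 × 0.665/200] = 0.05982.
- Rejection probability = Φ[(0.105 − 1.96 × 0.05913)/0.05982] = Φ(−0.182) = 0.428. The other tail is negligible.

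**Results at q = 30%.** The last column is a 5,000-run simulation of the Mann-Whitney test on log10 titre, with SD 0.5 and prior exposure adding 1.0 log10 (both assumed).

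| Prior exposure, young vs elderly | Observed rates | Spurious gap | False-difference rate, proportions | False-difference rate, titres |
|---|---|---|---|---|
| 2% vs 0% | 31.4% vs 30.0% | 1.4 points | 5.8% | 5.3% |
| 5% vs 1% | 33.5% vs 30.7% | 2.8 points | 8.0% | 7.8% |
| 10% vs 2% | 37.0% vs 31.4% | 5.6 points | 16.6% | 16.3% |
| 2% vs 10% | 31.4% vs 37.0% | −5.6 points | 15.6% | not run |
| 20% vs 5% | 44.0% vs 33.5% | 10.5 points | 42.8% | 43.3% |

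**Sensitivity to the assumptions.**
- q = 50%: 10% vs 2% gives 4.0 points and 10.0%; 20% vs 5% gives 7.5 points and 23.2%.
- q = 80%: 20% vs 5% gives 3.0 points and 9.2%.
- q = 95%: 20% vs 5% gives 0.15 × 0.05 = 0.75 points and 5.4%; the other splits lie between 4.9% and 5.6%.
- A smaller titre shift of 0.6 log10: 10% vs 2% gives 10.1%; 20% vs 5% gives 24.8%.
- No prior exposure: the Mann-Whitney rate is 4.5% to 5.6%, the nominal level within simulation error.
- Equal exposure in both groups: the gap is zero, although each rate is still raised. At 10% in both, the rate is 0.9 × 0.30 + 0.10 = 37% instead of 30%.

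**The case against.** **The schedule implies vaccine-naive participants.** This largely stands. Someone already vaccinated would not be receiving a first dose at Day 0, so it would go too far to infer that sites applying the protocol would knowingly enrol vaccinated people. What remains is that no criterion says so, and the argument does not touch past infection.

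**Exposure at entry is not shown.** This stands. A reader might infer widespread prior vaccination from the Background's statement that "China has received over 1.2 billion doses of the COVID-19 vaccine". That figure is dated June 29, 2022, whereas the enrolment date is July 1, 2021, so it says nothing about coverage at entry. Nor does "Participants will be recruited exclusively from two designated COVID-19 vaccination hospitals" show it: such hospitals are where people come to be vaccinated. Neither is evidence for this point.

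**The plan does not label anyone a responder.** Correct. One might read the plan as counting pre-existing antibody as vaccine response, but it only describes rates and titres by visit and defines no responder or seroconversion endpoint. The difficulty lies in the between-group comparison, not in a label.

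**Baseline titres are themselves an outcome, so an imbalance would be visible.** True, but displaying baseline values does not take the affected participants out of the later rates and tests.

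**Handling of baseline-positive participants belongs in an SAP, and all-comers is a defensible main set in a real-world trial.** An SAP could add a rule, and none is at hand. Even so, the eligibility lists, the FAS and PPS definitions and the between-group comparisons are fixed in this protocol. Followed as written, they keep baseline-positive participants in. All-comers remains useful, but as the companion result.

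**Conclusion.** The point holds as a possible bias in a secondary endpoint, not as a demonstrated one. Nothing in the protocol's eligibility or immunogenicity rules separates antibody present at Day 0 from antibody raised afterwards, and the age contrast has no randomisation to fall back on.

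The size and direction cannot be determined from the document. Under the assumptions above, the effect is trivial if prior exposure is rare, similar by age, or met by near-complete naive positivity. It becomes material at roughly 10% against 2% where naive positivity is low. The claim that prior immunity has created or hidden an age difference in this trial would go beyond the text. The primary safety analysis is unaffected. Because the Day 0 assay can settle the matter, this is an improvement worth making rather than a flaw that undermines the trial.

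**What to change.** Recruitment is recorded as complete, so the change is to the analysis:

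1. Report Day 0 seropositivity for neutralizing and anti-RBD antibody by age group, using the same cut-off that defines a positive result at follow-up.
2. Run the main immunogenicity comparison in participants negative for both antibodies at Day 0 with no recorded prior SARS-CoV-2 infection or COVID-19 vaccination. Medical history is taken at screening; where it does not cover these items, report the status as unknown.
3. Keep the all-comers FAS result as a sensitivity analysis.
4. Leave the Safety Set unchanged.

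The cost is one filter on data already collected, and a slightly smaller immunogenicity set if any participants are baseline positive. If none are, the two results differ only by anyone excluded on recorded history. A negative Day 0 titre does not rule out past exposure with waned antibody, so the report should call the set baseline-seronegative rather than naive.

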## 3.8. Allocation and vaccine management

### 3.8.1. Allocation

The participants will be assigned to either the experimental or control group in a 2:1 ratio based on age.

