**Demographic analysis:**

The analysis of baseline demographic information will be based on the FAS population.

This includes a statistical description and comparison of baseline demographic information (including age, gender, BMI, laboratory test indices, and comorbidities) to measure comparability between the two groups. Summarized statistical data will be used based on the properties of the variables (continuous or categorical).

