**Primary analysis:**

The main endpoint of this study is the safety after vaccination, which involves the evaluation of AEs, SAEs, and laboratory test indices, and performed on the SS.

The AEs/SAEs occurring in the two groups within one month after each dose of vaccination will be statistically described as a categorical variable, and Pearson’s chi-square test or Fisher’s exact test will be used for intergroup comparisons. The AEs/SAEs of the different categories will be summarized in percentages. The laboratory test indices at each follow-up point will be statistically described as continuous variables, and the Mann–Whitney U test will be used for intergroup comparisons. The median values of the laboratory test indices for the two groups will be calculated at each follow-up point, as well as the corresponding intergroup differences and 95% CIs.

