**Pseudovirus neutralization test analysis**

Based on the FAS population, an equal number of participants were randomly selected from both groups, ensuring no significant intergroup differences in gender and age, and no missing values at baseline and follow-up points at the 2^nd^, 7^th^, 8^th^, 13^th^, and 16^th^ months. The analysis of antibody-positive rates and titers (pVNT_50_s) is in the same way as the **Secondary analysis** mentioned above.

(1) Correlation between pVNT_50_s and symptoms

The infection status within the two groups will be statistically described, and the corresponding pVNT_50_s will be treated as continuous variables. An intergroup comparison will be performed using the nested t-test, and the corresponding geometric means and 95% CIs will be provided.

(2) Correlations between wild-type SARS-CoV-2–specific pVNT_50_s and variant-specific pVNT_50_s

The pVNT_50_s measured at each follow-up point will be statistically described as continuous variables. The Kolmogorov–Smirnov test will be utilized to evaluate data normality, followed by the Pearson correlation test or the Spearman rank correlation test for correlation analysis.

(3) Correlations between different variant-specific pVNT_50_s

The pVNT_50_s measured at each follow-up point will be statistically described as continuous variables. The Kolmogorov–Smirnov test will be employed to evaluate data normality, followed by the Pearson correlation test or the Spearman rank correlation test for correlation analysis.

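### The elderly–young comparisons of titres, antibody-positive rates and AEs are fixed as unadjusted tests in a non-randomised design, and the one regression in the plan names no outcome and cannot adjust the titre difference

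*Protocol*

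**What the plan says.** **Design.** The Trial Summary describes allocation as open and non-randomised. Section 3.2.1 sets the groups: "The young group was aged 18–59 years, and the elderly group between 60–80 years". Section 3.8.1 confirms it: "The participants will be assigned to either the experimental or control group in a 2:1 ratio based on age". Section 3.6 gives 200 elderly and 100 young participants.

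**Comparisons (section 3.10.2).**
- AEs, under Primary analysis: "Pearson’s chi-square test or Fisher’s exact test will be used for intergroup comparisons".
- Antibody positivity, under Secondary analysis: "The antibody-positive rates at each follow-up point in the two groups will be statistically described as categorical variables", with the same pair of tests.
- Titres, under Secondary analysis: "The antibody titers at each follow-up point in the two groups will be statistically described as continuous variables". The groups are then compared by the Mann–Whitney U test, with medians, group differences and 95% CIs.

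Neither paragraph mentions a covariate.

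**Baseline variables.** The Demographic analysis paragraph compares age, sex, BMI, laboratory indices and comorbidities "to measure comparability between the two groups". It does not say what happens if the groups are not comparable.

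**Regression.** The general principles in section 3.10.2 describe a univariate logistic screen of baseline characteristics at P<0.1, followed by a multivariate logistic regression reported as odds ratios. The dependent variable is not named, and neither the Primary nor the Secondary analysis paragraph refers to this model.

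**Pseudovirus subset.** Here the plan does ask for balance: participants are selected "ensuring no significant intergroup differences in gender and age".

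**The concern.** Every comparison between the groups is observational. Sex and BMI may differ between the young and elderly volunteers at two hospitals, and either may be related to reactogenicity or antibody response. If so, an unadjusted difference mixes the age-group contrast with those factors.

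The plan half recognises this. It treats sex as something to balance in the pseudovirus subset, but leaves it alone in the main safety and titre comparisons. Elsewhere it relies on a baseline significance test. Such a test answers a different question: whether an imbalance is larger than chance would produce, not whether it is large enough to shift the result.

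The regression does not close the gap. A logistic model needs a binary outcome and returns odds ratios, so it cannot adjust a difference in continuous titres. For AEs or positivity it could help, but with no outcome named and covariates picked by P value, which adjusted result will be reported is not settled before the data are seen.

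**Working it through.** **The plan's own figure.** Section 3.6 states 300 participants at 2:1, and 200/100 = 2 checks. No effect size, SD, event rate or power is given, so the number itself cannot be reproduced.

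**Step 1. How large a sex imbalance passes the baseline test?** Inputs: 200 and 100 participants and two-sided 5%, all from the protocol; a female share near 50%, assumed.

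Largest non-significant difference = 1.96 × √[0.25 × (1/200 + 1/100)] = 1.96 × √0.00375 = 1.96 × 0.0612 = 0.12, or 12 points. With a share near 30% it is 1.96 × √[0.21 × 0.015] = 0.11.

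**Step 2. Effect on the AE difference.** Shift = imbalance × effect of sex on AE risk. With an assumed 10-point higher risk in women: 0.12 × 0.10 = 0.012, or 1.2 points.

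For scale, the 95% half-width of the AE difference at 20% incidence is 1.96 × √[0.16 × 0.015] = 0.096, about 10 points. At 50% incidence it is 12 points.

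**Step 3. Effect on the titre difference**, in SD of log titre. SE = √(1/100 + 1/200) = 0.122 SD. The difference detectable with 80% power is (1.96 + 0.84) × 0.122 = 0.34 SD. The imbalances and sex effects below are assumed.

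| Sex imbalance | Sex effect | Bias | Two-sided rejection if there is no group effect |
|---|---|---|---|
| 10 points | 0.3 SD | 0.03 SD | 5.7% |
| 20 points | 0.5 SD | 0.10 SD | 12.9% |

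The second row exceeds the 12-point threshold, so the baseline comparison would normally flag it. Even then the plan attaches no adjustment of the titre difference to that flag.

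**Step 4. Can exact age be added to the group comparison?** Take ages uniform on 18–59 and 60–80 at 1:2 (assumed).
- Between-group variance: (1/3)(2/3)(70 − 38.5)² = 220.5.
- Within-group variance: (1/3)(41²/12) + (2/3)(20²/12) = 46.7 + 22.2 = 68.9.
- Total: 289.4.

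With age and the group indicator in one model, the variance of the group estimate is inflated by 289.4/68.9 = 4.2, so its SE roughly doubles. The groups share no ages, so the estimate would also rest on extrapolation.

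**Step 5. What the group cut costs if the aim were an age trend.** Share of information kept = between-group variance / total variance, for a linear age effect and uniform ages, with the elderly at 60–80.

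| Young group | Mean-age gap | Between | Within | Kept | Lost |
|---|---|---|---|---|---|
| 18–40 | 41.0 | 373.6 | 35.7 | 91% | 9% |
| 18–59 | 31.5 | 220.5 | 68.9 | 76% | 24% |
| 50–59 | 15.5 | 53.4 | 24.5 | 69% | 31% |

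**The case against.** **The plan does contain a multivariable step.** This stands in part. A reader might infer that the baseline variables are ignored altogether. The documents do not support that: the logistic regression could serve AEs or antibody positivity. What remains is that its outcome is unnamed, its covariates depend on P values, and it cannot reach the titre difference.

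**Adjustment is a matter for the analysis plan.** Model details such as knots or reporting ages are. But the protocol is not silent here: it names the tests for these comparisons, and they are unadjusted.

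**The age cut is the design.** This stands. A reader might infer that the plan throws away about a quarter of the age information. The protocol recruits two age groups and asks about people aged 60–80; it promises no age slope. The quarter is also only one scenario within a range of about 9% to 31%, all under a linear effect and uniform ages that the documents do not state. Nor is exact age an imbalance to be removed, since it defines the groups.

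**The bias is small and no imbalance is documented.** This also stands: 1.2 points is well inside a half-width of 10 to 12 points. It limits the weight of the point but does not remove it, because the remedy needs no new data.

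**Choice of covariates is debatable.** True. Comorbidity, and to some degree BMI, may be partly a consequence of ageing, so adjusting for them changes the question. That is a reason to settle the list beforehand.

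**Conclusion.** The point holds in a limited form. In a non-randomised comparison, the protocol fixes unadjusted tests for AEs, positivity and titres, although sex and BMI are on hand. Its only regression has no stated outcome, selects covariates at P<0.1, and cannot adjust the titre contrast.

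The likely size is modest: about 1.2 points on the AE difference at a 12-point sex imbalance, and 0.03 to 0.10 SD on titres in the cases tried. These figures rest on assumed sex effects and assumed imbalances; the true bias cannot be known from the document. The stated tests are not invalid as crude comparisons. An adjusted contrast should stand beside them.

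**What to change.** 1. Keep the stated tests. Beside them, prespecify an elderly–young contrast adjusted for sex and BMI with 95% CI: linear regression of log10 titre (back-transformed, an adjusted ratio of geometric means) and logistic regression for any AE after a dose.
2. Name the outcome of the logistic regression in the general principles of section 3.10.2. List its covariates in advance in place of the P<0.1 screen.
3. Do not enter exact age and the group indicator in the same model. If an age trend is of interest, report continuous age as a separate, supplementary model.
4. State in one sentence whether comorbidity is left out of the main adjusted contrast, and why.

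Cost: analysis work only, since sex is recorded and BMI follows from the height and weight taken at screening. The downside is some reliance on a regression model, and an adjusted summary on a different scale from the median difference; reporting both side by side deals with that.

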### 3.3.2. Intervention assignment

Both the experimental and control groups will receive two doses of the inactivated COVID-19 vaccine, administered on day 0 (baseline) and day 25±3. A third booster dose will be given 6 months after the second dose.

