## 3.5. Participant timeline

Figure 1. The schedule of enrolment, interventions, and assessments.

| **Visits** | **Screening** | **V1** | **V2** | **V3** | **V4** | **V5** | **V6** | **V7** | **V8** | **V9** |
| --- | --- | --- | --- | --- | --- | --- | --- | --- | --- | --- |
| **Timepoint (month)** | **Day**  **-21~0** | **Day 0** | **1^st^** | **2^nd^** | **4^th^** | **7^th^** | **8^th^** | **10^th^** | **13^th^** | **16^th^** |
| **Time window (day)** |  | **± 3** | **± 3** | **± 15** | **± 15** | **± 3** | **± 15** | **± 15** | **± 15** | **± 15** |
| **ENROLMENT:** | | | | | | | | | | |
| Informed consent | × |  |  |  |  |  |  |  |  |  |
| Eligibility screen | × |  |  |  |  |  |  |  |  |  |
| Demographical characteristics | × |  |  |  |  |  |  |  |  |  |
| Medical history | × |  |  |  |  |  |  |  |  |  |
| Urine pregnancy test  (reproductive women) | × |  | × | × | × | × | × | × | × | × |
| Height, weight, blood pressure | × |  |  |  |  |  |  |  |  |  |
| Underarm temperature | × |  |  |  |  |  |  |  |  |  |
| Lab tests & Images*^#^* | × |  |  |  |  |  |  |  |  |  |
| **INTERVENTIONS:** | | | | | | | | | | |
| Allocation |  | × |  |  |  |  |  |  |  |  |
| Vaccination |  | × | × |  |  | × |  |  |  |  |
| 30 minutes’ observing |  | × | × |  |  | × |  |  |  |  |
| **ASSESSMENTS:** | | | | | | | | | | |
| Lab tests*** | × |  | × | × | × | × | × | × | × | × |
| Distribute/recycle diary cards |  | × | × | × | × | × | × | × | × | × |
| Safety (AEs) |  | × | × | × | × | × | × | × | × | × |
| Safety (SAEs) |  | × | × | × | × | × | × | × | × | × |
| Concomitant care |  | × | × | × | × | × | × | × | × | × |
| Humoral immunoassays |  | × | × | × | × | × | × | × | × | × |

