# 7. APPENDICES

## *7.1 Revision History*

| **Version** | **Date** | **Amendment Text** | **Description** |
| --- | --- | --- | --- |
| 1.1 | March 6, 2020 | **Vaccination plan adjustment:**  The original statement “the participants will complete two doses of inactivated COVID-19 vaccine on day 0 and day 25±3” was modified to “the participants will receive a third dose of recombinant protein subunit vaccine 6 months after completing their two-dose regimen of inactivated COVID-19 vaccine.” | Due to the current pandemic, the national public health policy now mandates the administration of a third booster dose for vaccination. |
|  |  | **Follow-up time adjustment:**  Follow-up assessments are scheduled at the 1^st^, 3^rd^, 6^th^, and 9^th^ months following the administration of the two vaccine doses. The timing was adjusted to the 1^st^, 2^nd^, 4^th^, 7^th^, 8^th^, 10^th^, 13^th^, and 16^th^ months after the initial vaccine dose. | We need to conduct follow-up assessments in the 1^st^, 3^rd^, 6^th^, and 9^th^ months following the final vaccination to assess its safety and immune protection. |
| 2.0 (Final) | January 26, 2022 | **Items of laboratory test adjustment:**  Blood routine, liver and kidney function, blood glucose, blood lipids, and coagulation function will be tested at each follow-up point, adjusted to only test liver and kidney function, blood sugar, and blood lipids starting from the 7^th^ month (3^rd^ dose of vaccination). | The primary objective of performing blood routine and coagulation function tests is to assess safety post-vaccination. Following the initial two vaccine doses, no adverse reactions associated with coagulation or blood count were observed among the participants. The majority of the project participants are elderly individuals who are resistant to frequent and extensive blood collection, consequently leading to a reduced willingness for follow-up. To ensure compliance with follow-up procedures, the blood routine and coagulation function tests were omitted without compromising the scientific integrity of the project. |

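### Titres about one month after doses 2 and 3 are compared by nominal visit with ±15-day windows, so a difference between the age groups in mean sampling day would enter the age contrast

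*Protocol*

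**What the plan says.** **Visit clock.** Protocol 3.4.2 schedules the antibody samples at baseline and at months 1, 2, 4, 7, 8, 10, 13 and 16, counted in "months after the first vaccination in each study group". The revision history (7.1) gives the reason for this calendar: assessments are wanted at 1, 3, 6 and 9 "months following the final vaccination to assess its safety and immune protection". Time since the latest dose is thus the scale of interest after dose 3.

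**Windows.** In the schedule table (3.5), vaccination falls at V1 (day 0), V2 (month 1) and V5 (month 7), each with ±3 days. V3 (month 2) and V6 (month 8), the samples about one month after doses 2 and 3, have ±15 days.

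**Dose timing in the text.** Section 3.3.2 has the two inactivated doses "administered on day 0 (baseline) and day 25±3", and then: "A third booster dose will be given 6 months after the second dose". This differs from month 1 ±3 days and month 7 ±3 days in the table.

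**Analysis.** Section 3.10.2, Secondary analysis, groups the results by nominal visit: "The antibody titers at each follow-up point in the two groups will be statistically described as continuous variables". The age groups are then compared at each visit with an unadjusted Mann-Whitney test. Neither adjustment for nor grouping by actual sampling day is mentioned. The pseudovirus titres, which include months 2 and 8, follow the same method. The per-protocol set (3.10.1) excludes by number of follow-ups attended, not by departure from a window.

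**Groups.** Allocation is open, non-randomized and by age (Trial Summary; 3.8.1), with 200 elderly and 100 younger participants planned (3.6).

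**The concern.** Antibody titres change in the weeks after a dose. A sample drawn two weeks after the dose and one drawn seven weeks after it do not measure the same thing, yet both can carry the label V3 or V6. Randomization would make the mean sampling day similar between arms. Here the groups are defined by age, and nothing in the design balances attendance within the window. If one group comes later on average, the unadjusted comparison attributes the resulting titre difference to age. Immunogenicity in people aged 60 to 80 is a stated objective (2.2), so this contrast matters even though it is secondary.

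**Working it through.** The protocol states no range for time since dose, so there is no figure to reproduce. The check has two parts.

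**1. Time since dose allowed by the schedule**

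Shortest = earliest visit day minus latest dose day. Longest = latest visit day minus earliest dose day. A month is taken as 30.44 days (assumption).

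- V3: 60.9 ± 15 = day 45.9 to 75.9.
- V6: 243.5 ± 15 = day 228.5 to 258.5.

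| Dose timing used | Dose 2 (day) | Dose 2 to V3 | Dose 3 (day) | Dose 3 to V6 |
|---|---|---|---|---|
| Table in 3.5 | 27.4 to 33.4 | 12.4 to 48.4 | 210.1 to 216.1 | 12.4 to 48.4 |
| Text in 3.3.2 | 22 to 28 | 17.9 to 53.9 | 204.6 to 210.6 | 17.9 to 53.9 |

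The text gives no window for dose 3, so exactly six months (182.6 days) is added to the dose 2 range. With 30-day months the ranges are 12 to 48 and 17 to 53 days. Either timing alone spans 36 days. V2, the sample one month after dose 1, has a ±3-day window and lies about 27 to 33 days after that dose, so it is not affected.

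**2. What a difference in mean sampling day would do**

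None of these inputs is in the protocol except the group sizes and the two-sided 0.05 level: half-life h = 45 days (range 30 to 90), ln-titre SD 1.0, sampling days uniform over the 30-day visit window, no true age effect.

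- GMT ratio = 2^(−shift/h).
- SD of sampling day = 30/√12 = 8.66 days. On the ln scale at h = 45 this is 8.66 × 0.693/45 = 0.133.
- SE = √(1.0² + 0.133²) × √(1/200 + 1/100) = 1.009 × 0.1225 = 0.1236.
- Rejection rate = 1 − Φ(1.96 − d/SE) + Φ(−1.96 − d/SE), with d = shift × 0.693/h.

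At h = 45:

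- 3-day shift: d = 0.046, d/SE = 0.37, rejection 6.6%.
- 7-day shift: d = 0.108, d/SE = 0.87, rejection 14%.

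| Mean shift | GMT ratio, h = 45 (h = 30; h = 90) | Rejection, h = 45 (h = 30; h = 90) |
|---|---|---|
| 0 days | 1.00 | 5% |
| 3 days | 0.96 (0.93; 0.98) | 7% (9%; 5%) |
| 7 days | 0.90 (0.85; 0.95) | 14% (25%; 7%) |

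A separate calculation using the relative efficiency of the Mann-Whitney test (0.955), SD 1.0 and a 60-day half-life gives 7.5% for a 5-day shift and 15% for a 10-day shift, which is in line with the table.

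Scatter that is equal in both groups costs little: the factor 1.009 is a 0.9% larger SE (2.0% at h = 30, 0.2% at h = 90).

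**The case against.** **The windows are the same in both groups, so there is no bias unless mean attendance differs, and nothing shows that it does.** This stands. A reader might infer from 7.1 that elderly participants come later, because it says they resist frequent and extensive blood collection. That passage concerns willingness to be followed up. It says nothing about the day of attendance, makes no comparison with younger participants, and explains why some tests were dropped. It is a reason not to take equal timing for granted, not evidence of unequal timing.

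**Counting from dose 1 does little harm.** This also stands, on the table's timing: months 8, 10, 13 and 16 less month 7 give the intended 1, 3, 6 and 9 months, and the clock adds only the ±3 days of V5. The ±15-day window is the main source of spread.

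**A 7-day mean shift is large.** Fair: it is 0.8 of the 8.66-day SD of a uniform window. At 3 days the effect is slight. The sum also assumes steady decline from the early edge of the window, and the protocol gives no titre kinetics.

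**The statistical analysis plan may handle actual sampling days.** It may, and the absence of a covariate would not by itself be a finding. But the protocol is not silent: it fixes the grouping, the test and the analysis sets, and as written these ignore time since dose.

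**Conclusion.** The point holds for V3 and V6. The protocol permits a 36-day spread in time since dose (12 to 48 days by 3.5, or about 18 to 54 by 3.3.2) and compares non-randomized age groups there with a test that ignores it. A reader might join the two ranges and say 12 to 54 days. No single reading of the schedule gives that: it takes the lower end from one dose timing and the upper end from the other. The conflict between 3.3.2 and 3.5 is a separate defect that must be reconciled.

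The documents do not show that the titre comparison is biased, only that it is unprotected. Under the stated assumptions, the consequence runs from negligible (about 7% false positives at a 3-day mean difference) to moderate (14% at 7 days, 7% to 25% across half-lives). Loss of precision is not a reason to act. The comparison is secondary, and the primary safety analysis is unaffected by this point. The change is worth making because it is inexpensive and shows whether the problem exists.

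**What to change.** Leave the visits and the Mann-Whitney test as they are, and add to 3.10.2:

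1. A table of actual days since the most recent dose, by age group, at each visit.
2. For V3 and V6, a regression of log titre on age group with actual days since that dose as a flexible term (for example a quadratic or spline), reporting the adjusted GMT ratio with its 95% CI beside the Mann-Whitney result.

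Reconcile the dose timings in 3.3.2 and 3.5, so that time since dose has one planned value.

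**Cost.** Analysis wording only; recruitment is recorded as complete and no visit changes. The regression adds an assumption about how titre changes within the window. The flexible term relaxes it, but adjustment is weak if the groups' sampling days overlap little, which the table would reveal. It also needs recorded dose and sampling dates, a reasonable inference from the visit schedule that the protocol does not state.
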